
#### Analyses of Psychological and Physiological Mechanisms of the PA – Burnout/Vigor Relationship

Multiple mediation modelling will be used to examine the hypotheses that psychological (i.e., detachment, relaxation, mastery, control, relatedness, and positive affects experiences) and physiological (i.e., cardiorespiratory fitness) mechanisms partially or fully mediate the relationships between workplace PA or expressive activity on one hand and burnout and vigor on the other (H5). Two separate models will be generated with burnout and vigor as dependent variables. To handle the categorical independent variable (i.e., the experimental conditions), we will follow Hayes and Preacher’s [95] guidelines for calculating direct and indirect effects using a multicategorical predictor. Specifically, contrast coding will be used to examine the relative effect of workplace intervention (versus WLC), PA (versus Theatre condition) and PA with instructor using a need-supportive style (versus PA-TS) (see above). The scores of the mediating and dependent variables will be analyzed while controlling for the levels of measurement at baseline (i.e., the autoregressive effects). Autoregression allows the value of the variable at a previous time point to be statistical controlled, thereby reducing the likelihood of bias [96]. Bootstrapping procedures will be used to test the statistical significance of indirect effects of the proposed mediating variables [97]. Bootstrapping is a nonparametric resampling procedure for estimating indirect effects using adjusted (asymmetric) confidence intervals. This procedure is very useful in cases of multiple mediations, for which it is interesting to determine not only whether an indirect effect exists, but which mediator(s) contribute(s) significantly to the effect while controlling for other potential mediators. Point estimates and confidence intervals of relative indirect effects (total and specific) will be estimated from 5000 bootstrapped samples and 95% bias-corrected confidence intervals.

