### Recruitment process

Participants will be employees of the authors’ University. They will be recruited through email, posters and flyers posted on the university campus. Basic information about the intended program will be provided and those interested will be invited to complete a short online survey assessing their burnout and vigor at work, usual PA and some demographic information. Based on existing cut-off scores on the Shirom Melamed Burnout Measure (SMBM) and the Shirom Melamed Vigor Measure (SMVM) (obtainable at http://www.shirom.org/arie/index.html), inclusion criteria for participation will be: a) being above the first tercile of the SMBM (i.e., scoring ≥1.79 on the SMBM Burnout total score), b) being below the third tercile of the SMVM (i.e., scoring ≤ 5.00 on the SMVM Vigor total score). Exclusion criteria will be a) employees currently receiving or having received in the last six months pharmacological treatment for mental health disorders, b) having contraindications to exercise, and/or c) engaging in regular demanding physical training for competitive sports (i.e., Level 4 using the Saltin-Grimby PA Level Scale; see [69]). Eligible participants will receive a randomly assigned participant number and the informed consent form that they will have to read and sign. They will also be invited to complete a second online survey assessing some of the baseline measures: job characteristics, recovery experiences during leisure activities, work ability, job satisfaction, work performance. Participants will be randomized to one of the four conditions (see below). Then twice a week for ten weeks participants in the three activity conditions will take part in activities on the university campus. In the first session, a baseline cardiorespiratory fitness test will be conducted for all the participants.

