	− Needs satisfaction at work	✓	✓(T6)	✓	✓	
	− Workload at work			✓		
Manipulation check	− Instructors observed motivating style		✓(T8)			
	− *participants’ perception of the instructor’s motivating style*		✓(T8)			
	− Objective effort during sessions		✓(T6)			
	− Perceived effort during sessions			✓^a^		

^a^Variables only collected in intervention groups; ^b^Variables only collected in the waiting-list group

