##### Activity-related variables

Participants in the intervention groups will answer an additional eight-item questionnaire using the same bipolar visual analog scale as described above, in order to assess activity-related variables: *affect valence* (one item; “how do you feel after this session”, with the two opposing anchors “very bad” vs. “very good”) and *affect intensity* (one item; “how do you feel after this session”, with the two opposing anchors “low arousal” vs. “high arousal”), from Ekkekakis, Hall, Van Landuyt, and Petruzzello’s work [90]; five single-item measures assessing each of the *psychological recovery experiences* (see above); and the *perceived effort* (one item; “how intense was the effort you made during the last session?”, with the two opposing anchors “very slightly intense” vs. “very intense”).

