### Statistical analysis

#### Analyses of Primary and secondary outcomes

Between-arm differences in changes on the primary and secondary outcomes will be analyzed using generalized linear mixed models (GLMM) according to intention-to-treat and per-protocol principles. Intention-to-treat analyses [91] refer to the effect of treatment “as assigned”, meaning that all participants who are randomized to a condition will be included in the analyses, regardless of dropout or missing values. By contrast, per-protocol analyses refer to the effect of treatment “as received”, excluding only participants who have less than 50% compliance to the 20 sessions in the intervention. GLMM has several advantages over repeated measures ANOVA as it considers the hierarchical nature of the data and can accommodate missing data [92]. To distinguish between short- and long-term intervention effects, two separate series of GLMM analyses were performed for each outcome variable. Two time points (pre and post) were used to determine short-term intervention effects and four time points (pre, post, three- and four-month follow-ups) were used to examine long-term intervention effects. Regarding the short-term intervention effects, differences in changes on the outcome variables as a function of the group allocation will be assessed with models including group, time, and group x time interaction as fixed effects. For the group allocation, contrasts analyses [93] will also be carried out to test our hypotheses (H1 – H4) specifically. For that, three contrasts will be computed. The first one will compare the WLC condition with the Theatre condition, PA-TS and PA-NSS conditions (respectively coded as − 0.75, + 0.25, + 0.25, + 0.25) to test whether doing a leisure activity (PA or Theatre conditions) at the workplace leads to a reduction in burnout and an improvement in vigor (H1a, H1b). The second contrast will compare the Theatre condition with the PA-TS and PA-NSS conditions (respectively coded as − 0.667, + 0.333, + 0.333, while WLC will be coded 0) to test whether PA is more effective than theatre condition (H2) in reducing burnout and improving vigor. Finally, the third contrast will compare the PA-TS condition with the PA-NSS condition (respectively coded as − 0.50, + 0.50, while WLC and Theatre conditions will be coded 0) to test whether the positive effect of PA is more pronounced when the instructor uses a need-supportive style (H3). The same analyses will be performed to examine if the effects of the intervention are still effective three months (T12) and six months (T13) after the end of the intervention period. Since there are more than two-time measurements per participant, we will allow random intercepts for participants and random linear slopes for the repeated measurements at the level of participants. These random effects will allow us to estimate each participant’s outcome variables and the rate of change of these outcomes over time. In all analyses we will control for a number of variables that could influence participants’ outcomes. These include job characteristics, and needs satisfaction-frustration at work. Finally, an estimate of the effect size for each outcome will be reported using the conditional pseudo R^2^, which will be computed using the MuMin package of the R software [94].

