#### Analyses of Moderators

To examine whether participants’ experiences (i.e., detachment from work, relaxation, mastery, control, relatedness, or positive affects) during sessions moderate their well-being trajectories (H6c), a model comparable to the aforementioned models will be tested, except that the six experiences will be added as between-factors to the model and will also be modeled to interact with time (i.e., cross-level interaction). In these analyses, we will use each individual’s mean scores of the experiences during the 10 weeks of the intervention. Such a model, already used previously [66] will test if participants’ rate of change in well-being over time varies as a function of their average recovery experiences during the Nordic walking/ Theater sessions. To test if participants’ compliance to the intervention moderates their well-being trajectories (H7), we will also use a multilevel modelling framework. Two models will be tested for burnout and vigor respectively. This model is equivalent to the model testing weekly trajectories (see above), except that “compliance” will be added as a fixed factor in the model and will interact with other terms. This analysis strategy testing the moderation effect of compliance has been used in a study with a similar protocol design [66].

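### Positive affects (H5f) and session compliance (H7) exist only in the activity arms, so their waiting-list terms, and any baseline-adjusted positive-affect path, cannot be fitted as written

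*Protocol article*

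**What the plan says.** **Mediation (H5).** The section on psychological and physiological mechanisms names as mediators "psychological (i.e., detachment, relaxation, mastery, control, relatedness, and positive affects experiences) and physiological (i.e., cardiorespiratory fitness) mechanisms". It plans one multiple-mediation model for burnout and one for vigor, with each mediator judged while the others are held in the model. It says that "contrast coding will be used to examine the relative effect of workplace intervention (versus WLC", followed by PA against Theatre and PA-NSS against PA-TS. It then adds: "The scores of the mediating and dependent variables will be analyzed while controlling for the levels of measurement at baseline".

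**What is collected.** In Table 1, positive affects have a tick only in the weekly column (T1-T10); the T0 and T11 cells are empty. The tick carries footnote a, "Variables only collected in intervention groups". The section on activity-related variables agrees: "Participants in the intervention groups will answer an additional eight-item questionnaire", and the two affect items ask how the person feels after the session.

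**Compliance (H7).** The section on moderators takes the weekly trajectory model, which contains all three contrasts, and says that compliance "will be added as a fixed factor in the model and will interact with other terms". Under Measures, compliance comes from attendance registers kept by the instructors of the three intervention groups. The WLC arm has no sessions.

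**Fitness.** Under Recruitment process: "In the first session, a baseline cardiorespiratory fitness test will be conducted for all the participants". Under Measures, the repeat test comes at the start of the final session. Table 1 ticks fitness at T0 and T11 with no intervention-only footnote.

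**The concern.** The article fixes both the model and the collection schedule, and for two variables the two do not fit together. A path adjusted for the mediator's baseline needs a T0 value, and positive affects have none. A contrast with WLC needs WLC values, and there are none for positive affects or for compliance.

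At stake is H5f and, depending on how missing values are handled, every WLC indirect effect in H5. Mediation is the third stated objective of the trial and is listed among its strengths. If the conflict stands, the analyst must decide after seeing data whether to drop positive affects, drop the WLC arm or invent a compliance value for it. Each choice answers a different question.

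**Working it through.** **Inputs.** 140 participants, 35 per group (Sample size). Contrast 1 codes: WLC −0.75, and +0.25 for each of Theatre, PA-TS and PA-NSS (Analyses of primary and secondary outcomes). Seven mediators, three contrasts, two outcomes.

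**The plan's own figure.** With f = 0.35/2 = 0.175, alpha 0.025, power 80%, four groups, two time points and correlation 0.5, a repeated-measures group × time test needs 111 participants, or 112 when balanced (28 per group). 112 × 1.25 = 140, as stated. Only the arm size of 35 is used below.

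**Step 1: availability in WLC, from Table 1.**

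| Variable | T0 | T11 | WLC values |
|---|---|---|---|
| Detachment, relaxation, control, mastery, relatedness | yes | yes | yes (free-time questionnaire; only the weekly version is limited to the activity arms) |
| Cardiorespiratory fitness | yes | yes | listed, but tests are placed in sessions |
| Positive affects | no | no | none |
| Compliance | – | – | none |

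**Step 2: the positive-affect path.** A specific indirect effect is a × b, where a is the path from contrast to mediator and b the path from mediator to outcome. For contrast 1 and positive affects, a compares the activity arms with WLC, and no WLC value exists. Imputation or full-information likelihood cannot supply it, because no WLC participant ever has an observed value.
- Lost against WLC under any handling: 1 mediator × 2 outcomes = 2 effects.
- Without the planned baseline adjustment: 1 mediator × 3 contrasts × 2 outcomes = 6 effects.

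**Step 3: the joint model on complete cases.** Every WLC participant lacks positive affects, so 140 − 35 = 105 remain, and contrast 1 equals +0.25 for all of them, a multiple of the intercept.
- With all seven mediators: 1 intercept + 3 contrasts + 6 available baselines + 7 mediators = 17 columns; rank 16. Contrast 1 is not estimable.
- Without positive affects: 1 + 3 + 6 + 6 = 16 columns on 140 participants; rank 16. Contrast 1 is estimable. This takes Table 1 at face value for fitness in WLC.

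Of 7 × 3 × 2 = 42 specific indirect effects, contrast 1 accounts for 7 × 2 = 14. On complete cases all 14 go: the 2 that no method recovers, plus 12 lost only through listwise deletion.

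**Step 4: H7.** Intercept and three contrasts, each alone and times compliance, give 8 columns. Each is crossed with 1, time and time², giving 8 × 3 = 24.
- *WLC compliance missing:* contrast 1 is constant and contrast 1 × compliance = 0.25 × compliance. Rank is 6 of 8 per time term, 18 of 24 overall. Contrast 1 and its compliance interaction are both lost.
- *WLC compliance set to 0:* contrast 1 × compliance is −0.75 × 0 = 0 in WLC and 0.25 × compliance elsewhere, which is 0.25 × compliance for everyone. Rank is 7 of 8, 21 of 24 overall. Contrast 1 is estimable; its compliance interaction is not.
- In both cases contrasts 2 and 3 and their compliance interactions are estimable. Compliance itself is estimable once the redundant interaction is removed.

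**The case against.** The strongest reply is that the damage is narrow. Six of the seven mediators are listed at T0 and T11 for all arms, and the recovery questionnaire asks about free-time activities, which WLC can answer. No missing-data rule is stated for the mediation model, so complete-case deletion is an assumption. H7 compares higher with lower attenders, which makes sense only for people who have sessions, so the undefined term is one the hypothesis does not need. The article is also condensed.

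Most of this stands as a limit on scope. It does not remove the conflict. The mediators, WLC contrast, baseline control and collection schedule are all stated outright and cannot all be met. Where the authors meant to confine a hypothesis to the intervention groups, as in H6c, they wrote so; the H5 and H7 analysis text has no such restriction.

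Several stronger readings are tempting, and the documents do not support them:
- *WLC has no fitness data.* Table 1 carries no restriction and the recruitment text says all participants are tested. The placement in sessions is an ambiguity, not proof of absence.
- *A quarter of the sample and 14 of 42 indirect effects are lost outright.* This holds only for the joint model on complete cases.
- *Setting WLC compliance to 0 makes compliance collinear with the WLC contrast.* Compliance varies within the activity arms, so it does not. Only the interaction is redundant.
- *The per-protocol analysis must be replaced.* Its rule, "excluding only participants who have less than 50% compliance to the 20 sessions in the intervention", can remove people only from activity arms. That is a known limitation of an analysis reported beside intention-to-treat. It does not stop a model from being fitted, and a complier-average estimate would be a preference with assumptions of its own.

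**Conclusion.** Wrong as written, within a narrow scope.

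- The baseline-adjusted positive-affect path cannot be fitted in any arm, and 2 indirect effects against WLC are not estimable by any method. This rests only on the collection schedule.
- A further 12 WLC indirect effects are lost if the seven-mediator model is fitted on complete cases. They are recoverable if positive affects leave that model, assuming WLC does take the fitness test.
- The compliance × WLC-contrast terms of H7, including those with time and time², are not estimable under either treatment of WLC compliance. The rest of what H7 asks can be estimated among the activity arms.
- The fitness schedule needs clarifying.

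The primary intention-to-treat comparisons of burnout and vigor use neither positive affects nor compliance and are unaffected.

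**What to change.** 1. **H5.** Take positive affects out of the mediation model that carries the WLC contrast, and keep the six mediators listed at T0 and T11. Test H5f in the three activity arms with contrasts 2 and 3, using each participant's weekly mean and no baseline term for that mediator. Alternatively, collect an affect item at T0 and T11 in all four arms. It would need rewording, since the present one asks about a session just finished, and it can serve only participants who have not yet passed T0.
2. **H7.** State that the model is fitted in the three activity arms with contrasts 2 and 3, and report the result as an association, because attendance is not randomized.
3. **Fitness.** Reconcile Table 1 and the recruitment text, which cover all participants, with the placement of both tests in the first and final sessions, which WLC does not attend. State whether and when WLC is tested. If it is not, fitness must also leave the WLC-contrast model.

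The cost is a few sentences of analysis text, or a few survey items. The downside is that H5f and H7 become narrower claims: under the wording fix, neither speaks to activity against waiting list.

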
### Physical Activity and Secondary Outcomes

In addition to burnout and vigor, we will assess the consequence of the different conditions on four secondary outcomes, to check whether PA might also have other positive consequences on important job-related variables. First, we will examine the effects of the intervention on *job satisfaction*. This variable refers to a “pleasurable or positive emotional state resulting from the appraisal of one’s job or job experiences” [44]. Thøgersen-Ntoumani et al. [28] showed that participants in a workplace PA program experienced greater levels of enthusiasm and relaxation at work during the afternoon when they carried out PA during lunchtimes compared to the days when they did not. Then, by referring to SDT [45, 46], we will examine the effect of the intervention on the quality of *work motivation*, namely on autonomous (when the professional activities are experienced as emanating from one’s self) or controlled (when they are experienced as emanating from internal or external pressures) motivation. Such motivations are important to study because they are related to a host of cognitive, affective and behavioral consequences such as well-being, job satisfaction, organizational commitment, workaholism, burnout and turnover intentions [47, 48]. We will also investigate the effect of PA intervention on *work ability*. This refers to the “physical, psychological, and social capability of a worker to perform and interact within their work, and the individual’s specific work demands, health conditions, and mental resources” [49]. It has been demonstrated that burned-out people report decreased work ability [50], and an intervention study [37] reported that a six-week physical activity program improved work ability. Finally, we will study the effect of the intervention on the self-reported *work performance*. This variable refers to work-related activities expected of an employee and how well these activities were executed [51]. A few previous studies [52, 53] have reported that more physically active employees reported higher self-rated work productivity, and that a walking program in the workplace over sixteen weeks [54] increased work-performance by the end of the intervention.*Hypothesis 4:* the PA intervention is effective in improving job satisfaction (H4a), autonomous work motivation (H4b), work ability (H4c), and work performance (H4d).

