### Sample size

Sample size calculations were based on an a priori power analysis based on a previous study carried out on similar primary outcomes in the workplace [37, 66]. This study has reported a positive effect of the PA intervention on the emotional exhaustion component of burnout, with a small effect size (η^2^ = 0.03; f = 0.176). According to this result, we conducted an analysis with G*Power software [70] examining the evolution of burnout and vigor depending on the conditions as inter-individual factors, with an moderate effect size of d = 0.35, a statistical power of 80%, a threshold of significance at *p* < 0.025 considering our two primary outcomes, a correlation of .5 across repeated measures, and a potential dropout rate of 25% for a 10-week program with 4 groups. The results of this analysis recommend recruiting a minimum of 140 participants, 35 per group.

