#### Analyses of Weekly trajectories

To investigate the trajectories of weekly variables over the intervention period (H6a, H6b, H6c), we will use growth models in a multilevel modelling framework. Two models will be tested for burnout and vigor respectively. They will contain a random intercept and a random linear slope for the occasion of measurement at the subject level. This random slope for occasion measurements will allow each participants’ growth trajectory over time to be estimated. A linear and quadratic effect of occasion measurements will be added as fixed effects to examine the linear and accelerated evolution of the outcomes over time. The three orthogonal contrasts will be added as fixed factors to the model, as well as their interaction terms with “time” and “time2”. Thus, we will examine if there is an effect of the intervention (H6a), the type of activity or need-supportive style (H6b) on the level of and rate of change in burnout and vigor over time. In all analyses we will control for variables that could influence participants’ outcomes, such as weekly needs satisfaction-frustration at work and weekly workload.

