### Implication for practice

The study presented is significant and has direct applications in practice. If proven to be effective, it will make a unique contribution to the promotion of leisure activities and more specifically to the PA carried out in the workplace for the improvement of employee well-being. Indeed, this cost-effective, theory-grounded, scientifically validated intervention will benefit companies and employees. In addition, this intervention will contribute to scientific knowledge by highlighting the effectiveness of PA with an instructor trained to support needs, and the psychological and physiological mechanisms responsible for well-being improvement. Results of this study could be used by researchers to design new research protocols, and also by practitioners to implement more highly efficient programs in the workplace, and to improve the well-being of employees.

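### The mediation hypotheses H5a–g are decided on about 40 specific indirect effects, each by an unadjusted 95% bootstrap interval and without an exploratory label

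*Protocol article*

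**What the plan says.** The Protocol article, under Analyses of Psychological and Physiological Mechanisms, plans two multiple-mediation models, one for burnout and one for vigor. Each contains six psychological mediators and cardiorespiratory fitness. The arms enter through the three contrasts of the primary analysis: activity versus waiting list, physical activity versus theatre, and need-supportive versus traditional style.

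Bootstrapping is the significance test for the indirect effects. The section values it because it shows "not only whether an indirect effect exists, but which mediator(s) contribute(s) significantly to the effect while controlling for other potential mediators". The level is fixed for total and specific effects alike: "Point estimates and confidence intervals of relative indirect effects (total and specific) will be estimated from 5000 bootstrapped samples and 95% bias-corrected confidence intervals". The section does call bootstrap intervals adjusted, but it explains this as asymmetric. That describes their shape and is not a correction for the number of tests.

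H5, at the end of the section that introduces the mechanisms, lets a mediator be supported on burnout, on vigor, or on both. The only allowance for multiplicity in the article is in Sample size, where the threshold is "< 0.025 considering our two primary outcomes". Under Implication for practice, the trial is expected, if effective, to bring out "the psychological and physiological mechanisms responsible for well-being improvement".

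**The concern.** A mediator is called significant when one of its intervals excludes zero. Each of the seven has up to six chances, from two outcomes and three contrasts. The third objective asks which mechanisms explain the effect. Under this rule the answer can be a mediator picked out by chance.

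The risk depends on the two paths that make up an indirect effect: arm to mediator, and mediator to outcome. If both are zero, the test of their product is conservative and false positives are few. If one path is real, the interval in effect tests only the other, and each test then runs near its nominal 5%. The article's own rationale makes that case plausible: the activities are expected to produce recovery experiences, and these are expected to relate to burnout and vigor.

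**Working it through.** **Which level the plan uses elsewhere.** The inputs from Sample size are "an moderate effect size of d = 0.35" (so f = 0.35/2 = 0.175), "a statistical power of 80"%, correlation 0.5, four arms and 25% dropout. The short-term model has two time points.
- Noncentrality for the group-by-time test: λ = f² × N × m/(1 − ρ). With N = 112 this is 0.175² × 112 × 2/0.5 = 13.72, on 3 and 108 degrees of freedom.
- At 0.025, power is 0.808, and N = 112 is the smallest balanced total that reaches 80%. 112 × 1.25 = 140, the stated figure.
- At 0.05 the same calculation needs 96, and 96 × 1.25 = 120, which does not match.

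So 0.025 per outcome was in fact used to size the trial. It is not carried into the mediation section.

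**Count of tests.**
- Nominal: 7 mediators × 3 contrasts × 2 outcomes = 42 specific effects.
- Table 1 lists positive affects as a weekly measure only, with the footnote for variables collected only in the intervention groups. Their waiting-list contrast cannot be estimated for either outcome: 42 − 2 = 40.
- At 5% each, 42 × 0.05 = 2.1 false positives would be expected if every test ran at its nominal level.

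**Chance of at least one false mediator.** Under independence at exactly 5%, 1 − 0.95^42 = 88.4%. This is not the real risk, because the effects are correlated and the test is conservative when both paths are zero (about 0.7% per effect in simulation). The rule was therefore simulated with bias-corrected bootstrap intervals. The assumptions were 26 to 35 people per arm (140 × 0.75 = 105 completers, about 26 per arm), mediator correlation 0.3 to 0.5, outcome correlation 0.5 in size, and 200 to 300 trials per setting. Monte Carlo error is at most about √(0.25/200) = 3.5 points. The runs were simplified: they generally used 1,000 resamples instead of 5,000 and omitted the baseline terms.

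| True situation | At least one of 42 false |
|---|---|
| Both paths zero | 16–22% |
| Activity moves mediators 0.5 SD versus waiting list; no mediator affects outcome | 46–56% |
| Same, 1 SD | 57–65% |
| Other arm effects on mediators; no mediator affects outcome | 62–70% |
| Mediators predict outcome; arms do not move them | 51–79% |

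In one of these runs, dropping the two effects that cannot be estimated lowered a 56% rate to 53%.

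**Where the risk sits.** In a run with a 0.5 SD shift and an overall rate of 51%, the 14 activity-versus-waiting-list effects alone gave 48% and the other 28 gave 14%. At 1 SD the three figures were 64%, 64% and 15%.

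**Whether a correction helps.** With a 0.5 SD shift, testing the activity-versus-waiting-list contrast at 0.025/7 = 0.0036 per mediator cut its rate from about 44% to 3%.

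**The case against.** Several points on the other side are sound.
- The article ranks its outcomes as primary and secondary and places mediation third among its objectives. A reader might infer that there is no hierarchy at all. That is too strong: what H5 lacks is an adjustment or an exploratory label.
- A reader might extend the point to H4, H6 and H7. The documents do not support this. Their analysis sections state no level or decision rule, and a statistical analysis plan may well supply one. Only the mediation section fixes its own level.
- The 0.025 is a sample-size threshold for the primary outcomes, so using 95% for mediation does not contradict it. The fix borrows it as a natural level.
- No mediator shift is given in the documents, and when both paths are zero the risk is about a fifth. Most of the risk comes from 14 tests when activity moves the mediators, and positive affects have no waiting-list data for that contrast. If the mediators are entered jointly on complete cases, the waiting list drops out and 7 × 2 × 2 = 28 effects remain.
- A reader might infer that the total indirect effect must gate the specific ones. The documents do not require this, and such a gate can hide real mechanisms whose effects have opposite signs and cancel.
- The practice statement is conditional on the intervention proving effective.

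These points narrow the concern. They do not remove it: the 95% level, its use as a test for each mediator and the absence of an adjustment are written in the section itself.

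**Conclusion.** The concern holds for H5. The plan decides H5a–g on nominally 42 specific indirect effects (40 estimable), each at an unadjusted 95%, and nothing labels them exploratory. The chance of naming at least one false mediator is roughly 45–80% if one path is real and about 16–22% if both are null. These figures rest on assumed effect sizes, correlations and numbers per arm, so they show the order of size and are not a forecast. A reader might take the 88% independence figure as the risk, or conclude that a false mechanism is likely in every case. Neither follows, because the risk depends on which path is real. The consequence is confined to how mechanism findings are read. The primary efficacy conclusions do not change.

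**What to change.** In the mediation section, choose one of two routes before the data are analysed.
1. Name one contrast for H5 in advance. Within each outcome, apply Holm across the mediators that can be estimated for that contrast, at 0.025 per outcome, and label the remaining contrasts exploratory. Raise the number of resamples: at 0.025/7, two-sided, each tail holds only about 5000 × 0.0036/2 ≈ 9 of the planned 5,000.
2. Label all H5 mediation results exploratory, and report estimates with 95% intervals without calling individual mediators significant.

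Under Implication for practice, speak of candidate mechanisms unless the adjusted test succeeds.

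The cost is wording, a Holm step and more computing time; no new data are needed. The downside is that fewer individual mediators can be called significant, and under the first route mediation of the contrasts not named loses its formal test.
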